**Figure 2 F2:**
[figure not shown]
Process model of AMI development and pilot test.

Aim three: Examine the feasibility and acceptability of the AMI through a small-scale pilot study.

The AMI model will be designed for use by ASD community-based agencies to implement any EBP. However, for this pilot study, an EBP has been chosen *a priori*. This will allow for examination of each phase of the AMI and preliminary comparison between use of the AMI among agencies who participate in the pilot study. Specifically, an EBP to treat co-occurring anxiety disorders in children with ASD has been targeted due to the prevalence of anxiety disorders among school-age children with ASD and interest expressed by ACC partners.

Clinically significant anxiety disorders affect up to 80% of school-age children with ASD, causing heightened impairment above and beyond that caused by the ASD, and is the second most highly prevalent problem reported by parents [38-43]. Cognitive behavioral therapy (CBT) to treat anxiety disorders in children with ASD is considered evidence-based because multiple laboratories using rigorous research designs and methods (*e.g.*, randomized controlled trials) have found evidence supporting its use to alleviate or reduce anxiety symptoms or interference with large treatment effect sizes at post-treatment compared to control conditions [44-46]. Moreover, evidence suggests that intervening on children’s anxiety disorders has distal outcomes such as increasing social and daily living skills, and family functioning [44,47,48]. Preliminary data gathered from ASD Leaders indicate that anxiety is a significant problem for some of the school-age children being provided services at ASD community-based agencies. Interviews with ASD Leaders regarding current use of CBT by ASD-CPs found only two of the five agencies using CBT strategies to treat anxiety among school-age children with ASD. Of these, one agency reported using a manualized anxiety CBT developed for typically developing children with anxiety disorders rather than developed for children with ASD, and the other used exposure therapy (a component of CBT) but indicated that ASD-CPs were not certain about how to effectively use this practice with children with ASD. Using the AMI to implement a specific EBP to treat anxiety disorders in school-age children with ASD, aim three will evaluate the: feasibility of using the AMI within ASD community-based agencies; perceived fit, relevance, utility and compatibility of the AMI within ASD community-based agencies; training and support in the use of the AMI and AMI process materials; and observed fidelity of using the AMI to implement at EBP within ASD community-based agencies.

### Participants

Approximately 10 ASD Leaders (*e.g.*, clinical directors, executive directors), not participating in the ACC, will be recruited to participate in the AMI pilot study to test the feasibility and acceptability of the AMI. An agency will be eligible if it provides behavioral interventions, speech and language therapy, or social skills training to children with ASD and co-occurring anxiety disorders between the ages of 7–11 years. Agencies will be excluded if they do not provide services to children aged 7–11 years or do not serve any children with co-occurring anxiety disorders.

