**Figure 1 F1:**
[figure not shown]
**Preliminary conceptual model of the Autism Model of Implementation (Adapted from Aarons*****et al*****., 2011**[13]**; Damschroeder*****et al*****., 2009**[14]**; and Greenhalgh*****et al*****., 2004**[15]**).** Note. Discussions with ACC Partners yielded: factors to be emphasized (bolded) and added (bolded and italicized).

The work in the proposed project will proceed in three phases corresponding to three specific aims:

• Aim one: Assess agency antecedents and readiness factors, individual ASD-CP characteristics, and methods of implementing EBPs by ASD Leaders to identify factors that facilitate or hinder adoption and use of EBPs by ASD-CPs.

• Aim two: Develop the autism model of implementation (AMI) with the focus on identification, adoption, and use of EBPs within community-based agencies serving children with ASD.

• Aim three: Examine the feasibility and acceptability of the AMI through a small-scale pilot study. It is hypothesized that ASD-CPs will successfully complete each activity within each phase of the AMI to implement new EBPs within their ASD community-based agencies.

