### Participants

Development of the AMI will involve approximately seven ACC partners. The ACC will be comprised of three to five ASD-CPs who are responsible for directing, supervising, or training direct service providers within their agencies, one to two funding agency representatives (*e.g.*, regional centers, insurance companies, school districts) who are knowledgeable about how funding decisions are made for children with ASD, and an implementation researcher with expertise in studying implementation factors related to community agencies. A systematic recruitment strategy will be used in order to maximize the diversity of ACC partners, which is expected to increase the generalizability of the AMI to a variety of organizations, geographic locations, and providers.

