### Procedure

In collaboration with ACC partners, the review of the literature and aim one data will guide the development of the AMI. Specifically, results will be presented to ACC partners to obtain feedback and additional interpretation. Results and ACC partner feedback will be used to guide the development of the AMI and AMI materials (*e.g.*, needs assessment materials, *et al*.). Although the exact factors included in the AMI will require completion of aim one research activities, the AMI will likely include four phases: assessing needs of children with ASD and the agency, examining EBP factors to address those needs, addressing organizational factors and ASD-CP characteristics related to adoption, and identifying implementation factors, such as training, EBP flexibility, and ongoing support that will facilitate EBP use at the agency (Figure 1). For each phase, the AMI will have specific products, developed by the PI in collaboration with ACC partners, to be used by ASD Leaders in order to accomplish the goals of that phase. For example, ACC partners who collaborated in the development of this proposal reported that assessing need was an important step for an implementation model and that there was not a generalized, systematic assessment tool available for use by ASD-CPs. Therefore, an organizational assessment tool to identify common clinical targets of school-age children with ASD will be developed to support the implementation of the AMI. Table 1 outlines likely materials supporting AMI implementation.

**Table 1 T1:** AMI Process Materials for the AMI preliminary conceptual model

**AMI Phase**	**AMI Process Materials**
Phase 1: Assessing Need	· Assessment to identify common clinical targets of school-age children with ASD.
	· Assessment to identify agency need.
	· Guidance for locating EBPs to meet common clinical targets of school-aged children with ASD through targeted search engines cataloguing EBPs, such as National Standards Project, NREPP, Promising Practices Network, and PracticeWise.
Phase 2: EBP Factors	· Structured evaluation process to identify the goals, content, and structure of the EBP, rate the adaptability of the EBP, and training requirements.
	· Structured guide for evaluating the validity/evidence supporting the use of the EBP.
Phase 3: Adoption Factors (including preparing for uptake)	· Recommendations for enhancing agency antecedents and readiness for adoption of EBPs.

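### The pilot bars collaboration partners as individuals but not their agencies, so an agency whose staff helped build the AMI can become a test site

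*Protocol article*

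**What the plan says.** All references are to the Protocol article.

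- **Who may enrol (Aim three, Participants).** The pilot takes "Approximately 10 ASD Leaders" who are "not participating in the ACC, will be recruited to participate in the AMI pilot study".
- **Which agencies qualify (same section).** Inclusion: "An agency will be eligible if it provides behavioral interventions, speech and language therapy, or social skills training to children with ASD" with co-occurring anxiety, in the stated age range. Exclusion: "Agencies will be excluded if they do not provide services to children aged 7–11 years or do not serve any children with co-occurring anxiety disorders". There is no other agency-level criterion.
- **Who sits on the ACC (Aim two, Participants).** Among about seven partners are "three to five ASD-CPs who are responsible for directing, supervising, or training direct service providers within their agencies".
- **What the ACC does.** Aim two, Procedure says that the products for each AMI phase are "developed by the PI in collaboration with ACC partners, to be used by ASD Leaders". The section on the process of developing the AMI gives the partners a repeated role in revising the model and its materials. In the Aim three analysis plan, the final interview code list is settled by consensus with them, and results go to them for interpretation.
- **Level of measurement.** Aim three, Procedure places process and fidelity measures within each agency. The Aim three analysis plan scores the Stages of Implementation Completion (SIC), including discontinuation and censoring, by site.
- **Hypothesis (Background, specific aims).** Providers are expected to complete the AMI activities "to implement new EBPs within their ASD community-based agencies".

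**The concern.** An exclusion that protects independence should sit at the level at which the outcome is measured. Here the outcome belongs to the agency and the exclusion to the individual. An agency whose clinical director sits on the ACC can enter through its executive director. That agency may already know the model, have helped shape its materials, and have a stake in its success.

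Acceptability and completion are what the pilot exists to measure, so a lean towards the AMI at some sites bears directly on the main results. There is a second route as well. Because ACC partners agree the code list and interpret the findings, a partner could be interpreting interviews given by a colleague about a model that both of their names are attached to.

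A smaller, related point concerns the word new in the hypothesis. Nothing in the criteria addresses an agency that already uses Building Confidence, the manual chosen for the pilot. Completing the AMI there would not test adoption of a new practice. Likewise, leaders who took part in the Aim one focus groups, whose data feed the AMI, are neither excluded nor flagged.

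**Working it through.** The document states no figure on this point, so the check is a comparison of sections.

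1. **Grammar of the restriction.** In Aim three, Participants, the words about the ACC qualify the leaders. The next two sentences turn to agencies and do not carry the restriction over.
2. **Could a partner's agency meet the agency criteria?** Yes. The provider members of the ACC direct, supervise or train within agencies serving children with ASD. Nothing in the criteria separates those agencies from pilot agencies.
3. **Could that agency supply an eligible leader?** Yes, if it has more than one. The pilot section gives clinical directors and executive directors as examples of leaders, and an agency may have both.
4. **Does measurement fall on the agency?** Yes. The SIC-derived scores are the number of AMI phases completed, time in each phase, and proportion of process materials completed. All are tracked by site.
5. **Does the individual-level rule keep partners away from their own agency's data?** No. The PI and a research assistant code the transcripts, so partners do not code them directly. They do agree the final code list and interpret the results, and nothing sets aside data from a partner's own agency.
6. **Scale.** With about 10 leaders and, by assumption, one leader per agency, each site contributes 1/10 = 10% of the sample. The document gives no rate at which ACC-affiliated agencies would be recruited, so no expected number follows.
7. **Newness.** The hypothesis requires the practice to be new to the agency. The criteria do not ask about prior use of Building Confidence or of other CBT. However, the provider strategies survey (PSS), which covers use of practices and formal training in them, is given before and after implementation. Prior use can therefore be described from data already planned, provided that CBT and Building Confidence are among its items, which the article does not state.

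**The case against.** **The wording may simply be loose.** The article moves freely between leaders and agencies, so barring the ACC leader may have been meant to bar the agency. It is also a condensed account. This is fair as to intention. But the article does set out inclusion and exclusion rules at both levels, and the agency rules omit the ACC. If agencies were meant, the correction only records it.

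**The bias is not demonstrated.** This stands. The article contains no evidence that a partner's agency would rate the AMI more favourably or finish sooner. An agency already using some CBT might see less need and discontinue. The concern is a possibility that the rules leave open.

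**This is a feasibility pilot whose limits are acknowledged.** The analysis plan notes the lack of a control group and the small sample. No error rate is affected. But neither caveat tells a reader that some sites may have helped build what they are judging.

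**Two stronger readings are tempting and should not be made.**

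- From the size of the ACC, a reader might infer that a large share of pilot sites would come from partner agencies. That requires the maximum number of provider partners, each from a different agency, each agency having a further eligible leader, and all enrolling. None of these is given.
- The preliminary interviews "found only two of the five agencies using CBT strategies to treat anxiety among school-age children with ASD". A reader might project 2/5 = 40% onto the pilot and say that the practice would not be new to that share of sites. The same section describes what the two agencies did: one used a manual written for typically developing children, and the other used exposure therapy alone, with staff unsure how to apply it to children with ASD. Building Confidence would, on that description, still be new to both. The five leaders were also a convenience sample. The exact 95% interval for 2 of 5 runs from 5.3% to 85.3%, or 10 × 0.053 = 0.5 to 10 × 0.853 = 8.5 agencies in ten, which is too wide to plan on.

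**Conclusion.** The point holds for the level of the exclusion. As written, the rule permits an agency with an ACC partner to be a pilot site, and leaves that partner a part in settling the codes for and interpreting that agency's data. The consequence is for interpretation: acceptability and completion could look better than they would in agencies with no part in developing the AMI. The likely size is unknown. It depends on how many partner agencies have a second eligible leader and choose to enrol.

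The point about newness is secondary and narrow. It applies to agencies already using Building Confidence itself, for which the document gives no rate. It does not extend to agencies using other forms of CBT. A blanket exclusion of these would remove sites where the pilot practice is still new, and would narrow an already small sample. Nor can it be said that such agencies have little room to change on the PSS, since that survey is described as covering evidence-based practices generally, not CBT alone.

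**What to change.** **Main change.** Add one sentence to Aim three, Participants: no agency at which an ACC partner works is eligible for the pilot. Wording it by place of work avoids excluding agencies merely because a funder that pays for their services is represented on the ACC.

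**Secondary change.** Use the baseline PSS to list, for each site, prior use of Building Confidence and of other CBT for anxiety, and note whether the leader took part in Aim one. Show this beside each site's SIC and PSS results. Say in the text that a site already using Building Confidence does not test the hypothesis about new practices. Do not exclude sites for using other CBT or for Aim one participation. With about 10 leaders, a descriptive listing is more useful than subgroup results.

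**Cost.** The recruitment pool becomes slightly smaller. The listing needs no new data collection if the PSS covers these practices, and otherwise one added question at baseline.

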### Procedure

The AMI will be used to implement ‘Building Confidence,’ a manualized CBT for children with ASD and co-occurring anxiety disorders [49]. The PI is a co-author of the manualized intervention and will consult with the primary author throughout the pilot study to address EBP factors (*e.g.*, time available for training, billing procedures, *et al*.), organizational adoption-related factors, and factors facilitating implementation. The pilot test will involve a pre-post design. ASD Leaders will be asked to complete questionnaires and participate in interviews prior to and after implementation of the AMI. Measures of AMI implementation will involve process and fidelity measures within each agency.

### Data/measures

Data from the demographic survey, EBPAS, CSS, and PSS used during aim one will be administered at pre- and post-implementation of the AMI (see aim one for more information about these measures).

### Stages of implementation completion (SIC)

The SIC [50] is a time-to-event based observational measure of implementation progress that consists of eight stages relating to specific implementation milestones. These milestones include: engagement, consideration of feasibility, readiness planning, staff hired/trained, adherence monitoring processes in place, services and consultation begin, ongoing services, consultation fidelity monitoring and feedback, and competency. The milestones span the timeframe from the engagement stage where initial contact between interested parties occurs through the attainment of program competency stage. Stages extend from ASD Leaders through ASD-CPs in order to capture the multiple levels involved in implementation. The SIC is intended to be tailored to fit specific EBPs and implementation models, and can be modified to assess quality and fidelity of the stages of implementing the AMI. The measure authors have agreed to work with the PI to adapt the SIC to best reflect the phases and steps within the AMI. Analysis of the SIC involves a time-to-event modeling method.

### Individual interviews

Leaders will be interviewed prior to the AMI implementation to assess their perceptions of the AMI, including perceived fit, relevance, utility, and compatibility with their ASD agency. At post-implementation, interviews will assess perspectives about the AMI, including feasibility and acceptability, changes in agency process for implementing EBPs, and changes in ASD-CP practices. Individual interviews will take approximately 30 minutes.

### Analysis plan: Integration of qualitative and quantitative analyses

Repeated measures ANOVA for pre- and post-implementation questionnaires will be used to examine the changes that occurred during AMI. Due to the lack of a control group and the small sample sizes, interpretation of effect sizes will be examined.

The SIC will be analyzed with guidance from the measure authors and statistical consultant using the Cox proportional hazards time-to-event modeling method [51] within multiple stages. Analyses will replicate those used during the measure development. In particular, an outside observer (*e.g.*, research assistant) will track the dates of completion of each activity within each phase of the AMI in a stage-tracking database. From these data, three scores are derived: the number of AMI phases completed, the time spent in each AMI phase, and the proportion of AMI Process Materials completed in each phase. For sites that choose to discontinue implementation, the discontinuation date will be logged accordingly in the furthest phase that the site entered. If this occurs, the time spent in the final phase of the AMI is calculated between the date of the earliest activity within the phase and the date of discontinuance. If the observation period ends before the phase is completed but a site has not discontinued implementation, the observation will be treated as being censored (*e.g.*, standard time-to-event analysis).

Pre- and post-implementation interviews will be analyzed using a coding, consensus, and comparison methodology [52], which follow an iterative approach rooted in grounded theory [53]. Transcriptions will be independently coded by the PI and a trained research assistant at a general level in order to condense data into analyzable units. The coding will be reviewed by grant mentors and consultants. Transcriptions will be assigned codes based on a priori or emergent themes. Transcriptions may be assigned more than one code. Disagreements will be resolved through subsequent discussion between research team members. The final list of codes will be developed through consensus with ACC partners. Based on the codes, the process of axial coding will be used to generate a series of categories arranged in a treelike structure connecting segments into separate categories or nodes. Nodes and trees will be used to create a taxonomy of themes, including *a priori* and emergent categories and new, unrecognized categories. Results will be presented to ACC partners for interpretation.

Finally, methods for integrating qualitative and quantitative data for analyses will be the same as those used in aim one (see aim one for details).

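### Discontinuing sites get no separate status, so the time-in-phase score, and by inference the Cox model, do not separate quitting a phase from completing it

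*Protocol article*

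**What the plan says.** The rules are in the aim three section of the protocol article headed Analysis plan: Integration of qualitative and quantitative analyses. The SIC will be analysed "using the Cox proportional hazards time-to-event modeling method", stage by stage. From the logged activity dates, "three scores are derived: the number of AMI phases completed, the time spent in each AMI phase, and the proportion of AMI Process Materials completed", the last two phase by phase.

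Two rules govern sites that do not finish a phase:

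- If a site discontinues, "the discontinuation date will be logged accordingly in the furthest phase that the site entered". Its time in that phase is then the interval "between the date of the earliest activity within the phase and the date of discontinuance".
- If observation ends before the phase is complete "but a site has not discontinued implementation, the observation will be treated as being censored".

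The section also states: "Analyses will replicate those used during the measure development". That source is not reproduced. No event definition, failure code or competing outcome is given for a discontinued site.

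**The concern.** Aim three hypothesises that providers will get through every activity in every AMI phase. A site that abandons a phase is evidence against that hypothesis. Yet the plan gives such a site a closed duration and limits censoring to sites that have not discontinued. In the time score, a short value can therefore mean quick progress or early abandonment. In a Cox data set, a time that is not censored is ordinarily an event, so the natural reading makes a quit count like a completion.

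If quitters tend to leave early, the time results would look better because some agencies could not carry on. With about 10 sites, two or three discontinuations are enough to move the summaries noticeably.

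**Working it through.** The plan states no phase durations, no expected number of discontinuations and no observation length, so there is no figure of its own to reproduce.

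Inputs from the document: the Cox method, the three scores, the duration rule, the censoring rule, and the pilot size, "Approximately 10 ASD Leaders" (aim three, Participants). Inputs assumed: one leader per agency, hence 10 sites, and all times below.

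Step 1. Set the rules side by side.

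| How the site leaves the phase | Time assigned | Status assigned |
|---|---|---|
| Completes it | Time spent in the phase | Not spelled out; the natural event |
| Discontinues | First activity in the phase to discontinuance | None stated; outside the censoring rule |
| Still active when observation ends | Up to the end of observation | Censored |

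The first two rows differ in meaning, but nothing in the time score or the stated model rules keeps them apart.

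Step 2. Time score. Assume 7 completers at 70, 80, ..., 130 days and 3 quitters at 15, 25 and 35 days.

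- Completers only: 700 / 7 = 100 days.
- Pooled as written: (700 + 75) / 10 = 77.5 days.
- In general, with 3 quitters leaving at mean time m: (700 + 3m) / 10 = 70 + 0.3m. This is below 100 when m is below 100 and above it when m is above 100. At m = 130, the slowest completer's time, it is 70 + 39 = 109 days.

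So the direction of the shift depends on when quitters leave.

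Step 3. Event rate, if quits count as events. Site-days are 775 under either coding.

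- Quits counted: 10 / 775 = 0.0129 per site-day.
- Completions only: 7 / 775 = 0.0090 per site-day.
- Ratio: 10 / 7 = 1.43.

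Because the site-days cancel, this ratio depends only on the numbers of quitters and completers.

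Step 4. A second assumed set, to compare codings: 6 completers at 60, 75, 90, 100, 110 and 120 days, 3 quitters at 20, 30 and 40 days, and one site still active at 180 days.

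| Coding of the quits | Median time (days) | Share through the phase by day 180 |
|---|---|---|
| As finished | 75 | 9/10 = 90% |
| As censored (Kaplan-Meier) | 100 | 1 − 1/7 = 86% |
| As a competing outcome | 110 | 6/10 = 60% |

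The mean is 645 / 9 = 71.7 days over completers and quitters pooled, against 555 / 6 = 92.5 days for completers only. Censoring alone still reads 86% where 60% completed.

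Step 5. Range over the number of quitters among 10 sites (assumed quits at 20 to 60 days, completions at 60 to 150 days, one site active at 180 days).

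| Quitters | Pooled mean (days) | Completers' mean (days) | Apparent share through | True completion |
|---|---|---|---|---|
| 0 | 108.3 | 108.3 | 90% | 90% |
| 1 | 93.9 | 103.1 | 90% | 80% |
| 3 | 71.7 | 92.5 | 90% | 60% |
| 5 | 58.3 | 81.2 | 90% | 40% |

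The means should be compared within a row: in this construction each added quitter replaces the slowest completer, so the completers' mean falls too.

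**The case against.** The duration rule is not wrong in itself. First activity to discontinuance is the time the site actually spent in the phase, and a competing-risks analysis needs that same interval. The discontinuation date is logged, so the information that separates quitters from completers is kept. The event code is never stated, a condensed article may leave it to a fuller document, and the analysis to be replicated is not shown. All of this stands, and it is why the Cox part of the point is an inference. It does not remove the difficulty in the time score, which pools the two kinds of exit whatever code the model uses. Nor does it change the censoring sentence, which as worded leaves discontinued sites out.

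A reader might go further and infer that the SIC as a whole scores an early quitter like a fast completer. The document does not support that. The number of phases completed and the proportion of materials completed would still show that a quitter did not finish, and these scores speak most directly to the aim three hypothesis. Post-implementation interviews also assess feasibility.

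A reader might also infer that the rule always flatters the AMI. Step 2 shows that the time score can move either way.

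**Conclusion.** The point holds for the time-in-phase score and, by inference from the censoring rule, for the Cox model. Neither, as described, distinguishes completing a phase from abandoning it. If quitters leave before completers finish, phase times look shorter; if quits are coded as events, the apparent completion hazard is also too high. In the first illustration the mean is 77.5 instead of 100 days and the rate is 1.43 times as high. Late quitting would lengthen the time score instead. These sizes rest wholly on assumed times and numbers of quitters.

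The severity is moderate: it should be fixed. This is a single-arm pilot with about 10 leaders, no stated decision threshold on phase time, and two other SIC scores that are unaffected. It would be too strong to say that the plan expressly codes discontinuation as success, or that the feasibility conclusion as a whole is invalid.

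**What to change.** State three things in the aim three analysis plan:

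- The event in the time-to-event analysis is completion of the phase.
- Discontinuation is a competing event. Discontinued sites contribute time at risk up to discontinuance but do not count as events in the cause-specific hazard of completion. That hazard alone should not be turned into a proportion completing, for the reason shown in step 4.
- Time in phase is reported for completers, beside the number and timing of discontinuations among all enrolled agencies.

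Cumulative incidence curves for completion and discontinuation are optional at this sample size. The cost is a few sentences, since the dates are already to be logged. The downside is that reported feasibility may look slightly less favourable.
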